### Secondary endpoints

#### Pain

Using the smartphone technology [38] which downloads automatically, information on (a) pain characteristics (intensity, location, quality), (b) pain medications and non**-**pharmacological strategies used for pain, (c) health care visits will be collected in the pilot to test out the methodology and to determine whether there is any obvious effect of either intervention or its withdrawal, particularly if detrimental. This is important as the first outcome measure for trial 2b will be average pain intensity during the 2 observation periods.

#### Adverse events

The Clinical Report Forms (CRFs) for reporting adverse events will be trialled during this pilot to show efficacy in recording and reporting adverse events.

Daytime oxygen saturation will be collected before and after each intervention to determine whether there is any obvious effect of either intervention or its withdrawal, particularly if detrimental.

#### Lung function

Spirometry and lung volume will be collected before and after each intervention to determine whether there is any obvious effect of either intervention or its withdrawal, particularly if detrimental.

#### Quality of life data

Age appropriate versions (paediatric or adult) of the PEDS**-**QL quality of life measure [50], including the sickle module, will be collected at the beginning of trial and after each intervention to determine whether there is any effect of either intervention.

### Statistical analysis

The preliminary data on participant preference and physiology will be analysed at the end of this pilot phase and will be used to make a final decision about which intervention should be used for trial 2b (the Phase 2 study). This is a pilot phase; all statistical analyses will be treated as preliminary and exploratory and will mainly be descriptive [54]. We will investigate factors that influence recruitment rate, acceptability, adherence and loss to follow**-**up. The variability of outcome measures will be reported and any indication of improvement on any of the treatment will be explored informally: e.g. daily pain rate from the smartphone app, admissions to hospital for complications and laboratory parameters. The decision will be made primarily according to participant preference and, if this is at equipoise, on any apparent physiological benefits, e.g. higher daytime oxygen saturations, improved lung function or rates of adverse events. The cost implications will be assessed and relative long**-**term costs to the NHS will be taken into account if there is still equipoise.

The study will be reported in accordance with the CONSORT (Consolidated Standards of Reporting Trials) 2010 statement (Additional file 1) (or latest version if it is available at the time of reporting) [55]. A baseline table will be included to compare important demographic and clinical characteristics between those who started intervention 1 first and those who started intervention 2 first. In total there 3 time points, baseline, after intervention 1 and after intervention 2; all variables will be reported at all 3 time points. Any deviations from the original statistical plan will be incorporated, with full explanation, into a revised version of the protocol.

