**Methods/Design:**

This is a pilot cross**-**over interventional trial with the order of interventions decided by simple randomization. Ten adults (age over 18 years) and 10 children (aged between 8 and 18 years) with homozygous sickle cell disease (haemoglobin SS, HbSS), recruited regardless of symptoms of sleep**-**disordered breathing, will undergo overnight pulse oximetry and will have two interventions, overnight oxygen and APAP, for a week each in randomised order with a washout week between interventions. Participants will complete online diaries via an iPad throughout the 29 days of the study and will complete QOL questionnaires and have measurement of haematology, biochemistry, spirometry and lung volumes (adults only) at 3 time points, at baseline and after each intervention, as well as in-depth semi-structured qualitative interviews after each intervention, carried out by an experienced psychologist. Both qualitative and statistical methods will be used to analyze the data. The primary outcome is qualitative data looking at participant experience from the transcribed interviews after each intervention. The participant’s view on feasibility, acceptability and preference will specifically be explored. The QOL, laboratory and lung function data will be compared with baseline for each arm.

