There are 4 objectives for this study: (1) to assess whether overnight oxygen therapy or APAP is more acceptable to participants, (2) to assess whether there are any physiological or clinical benefits or risks of overnight oxygen therapy or APAP, (3) to assess the feasibility of using smartphone technology to collect daily information on site and severity of pain and (4) to identify the main cost drivers and potential cost implications of providing the intervention.

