### Participants

This pilot study will involve 20 participants, recruited regardless of symptoms of sleep**-**disordered breathing, which includes 10 children (age between 8 and 18 years) and 10 adults (age over 18 and above). All participants will be enrolled into the study for 29 days (i.e. 4 weeks).

Consenting participants with HbSS who are aged > 8 years and attend at Guy’s and St Thomas’ NHS Foundation Trust are eligible for this study. Participants will be excluded if they already have overnight respiratory support, if they have existing respiratory or decompensated cardiac failure or if they have any contra**-**indications to APAP therapy. Both inclusion and exclusion criteria are listed in Table 2.

**Table 2 Tab2:** Participant eligibility criteria for participation in the POMS2a trial

Inclusion criteria	
1	Recruitment will be through sickle cell clinics at Guy’s and St Thomas’ (including Evelina Children’s Hospital)
2	Age > 8 years
3	Informed consent with assent in accordance with the institutional policies (UK ethical committee) and European or US Federal guidelines must be signed by the participant or participant's parent or legally authorised guardian acknowledging written consent to join the study. Where appropriate, participants < 16 years will be requested to give their assent to join the study
4	HbSS diagnosed by standard techniques (HPLC, IEF and MS). Participating institutions must submit documentation of the diagnostic haemoglobin analysis
5	Able to speak and understand English
6	Participant or parent/guardian able to use iPad mini via wireless
Exclusion criteria	
1	Participant already on overnight respiratory support, or has used it in the past
2	Hospital admission for acute sickle complication within the past 1 month
3	Participant with > 6 admissions for acute sickle complications within the past 12 months
4	Existing respiratory failure
5	Decompensated cardiac failure
6	History of severe epistaxis
7	Trans-sphenoidal surgery, or trauma that could have left a cranio-nasopharyngeal fistula
8	Perforated ear drum
9	Bullous lung disease
10	Bypassed upper airway
11	Pneumothorax
12	Participant at increased risk of aspiration

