**Fig. 1 Fig1:**
[figure not shown]
Flow chart for the interventions and support from the respiratory physiologist

On day 1, the patient will attend the Day Care Unit at the hospital and data including baseline blood tests, PEDS**-**QL quality of life [50], daytime oximetry, will be collected. Adults will undergo lung function (spirometry and lung volume). The participant will be issued with an iPad mini with a validated smartphone app [38] for rating pain and symptom assessment and will be asked to complete daily data collection using this device for the duration of the whole study, taking approximately 5 minutes per day. They will be given an overnight oximeter to take home and will be asked to use this for 2 nights over the next week. The randomization codes will be provided at the start of the study by an independent statistician from the University of Southampton, who will use simple randomization to generate the order.

On day 8, the participant will have the first intervention (intervention 1), either oxygen or APAP, which will be delivered to their home and set up by the respiratory physiologist, or if they prefer, they can take the treatment home after explanation by the respiratory physiologist. They will be asked to use this for 7 nights and will have planned support calls (Fig. 1). The overnight oximeter will be collected by the respiratory physiologist and the data analysed. On day 15 the participant will return to the hospital Day Care Unit for medical assessment, blood tests, PEDS**-**QL quality of life assessment, daytime oximetry and the first qualitative assessment with lung function studies for the adults. Days 16**–**21 will be a washout phase with no intervention given, but ongoing daily data collection via the smartphone app on the iPad mini. On day 22 the participant will have the other intervention (intervention 2) installed at home and they will be asked to use this for the next 7 nights. On day 29, the participant will go to the Day Care Unit at the hospital for medical assessment, blood tests, PEDS**-**QL quality of life assessment, daytime oximetry and lung function tests (adults) and the second qualitative assessment. Adverse events and serious adverse events will be reported to the sponsor (Tables 4 and 5).

**Table 4 Tab4:** Laboratory findings to be reported to the sponsor within a maximum of 7 days

Variables	Measurement level that may be consider as adverse events
Haemoglobin	Fall of > 20 g/l from baseline is significant

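### The labels intervention 1 and 2 contradict their own definition, and the only quantitative comparison named is with Day 1, not oxygen against APAP with period allowed for

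*Protocol article*

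**What the plan says.** **Reporting.** The Statistical analysis section states: "In total there 3 time points, baseline, after intervention 1 and after intervention 2; all variables will be reported at all 3 time points". Just before that, it plans a baseline table to compare characteristics "between those who started intervention 1 first and those who started intervention 2 first".

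**Definition of the labels.** The Procedure section says that on day 8 "the participant will have the first intervention (intervention 1), either oxygen or APAP", and that the remaining device is intervention 2, installed on day 22. Table 3 follows the same usage, with intervention 1 under Days 8–14 and intervention 2 under Days 22–28.

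**Comparison.** The Abstract (Methods/Design) names one quantitative comparison: "The QOL, laboratory and lung function data will be compared with baseline for each arm".

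**Use of the data.** Objective 2 is "to assess whether there are any physiological or clinical benefits or risks of overnight oxygen therapy or APAP". The Statistical analysis section bases the choice of Phase 2 device first on what participants prefer. It then gives this fallback: "if this is at equipoise, on any apparent physiological benefits, e.g. higher daytime oxygen saturations, improved lung function or rates of adverse events". It also says that "all statistical analyses will be treated as preliminary and exploratory and will mainly be descriptive".

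**The concern.** The labels carry two meanings. In the Procedure section and Table 3 they are periods. In the baseline-table sentence they make sense only as devices, because under the period definition everyone starts with intervention 1. The reporting sentence that follows can be read either way. Read with the definition the article gives, it pools the two devices that the trial is meant to choose between.

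The comparison named does not match the decision. Choosing a device needs oxygen against APAP in the same participant, which is what a cross-over provides. A change from Day 1 contains the device effect plus anything else that moved since Day 1, such as practice at spirometry, regression to the mean or drift. The Lung function section and the saturation paragraph under Adverse events promise measurement before and after each intervention. Table 3 and the Procedure section, however, give daytime oximetry and lung function only at Day 1, Day 15 and Day 29, so nothing is scheduled just before the second device.

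At stake is the tie-break for the Phase 2 device.

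**Working it through.** The article gives no power, effect size or variance on this point, so there is no figure to reproduce. The check is the algebra of a two-period cross-over.

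**Inputs from the article**
- "This pilot study will involve 20 participants", of whom 10 are children and 10 adults (Participants). Lung volumes are measured in adults only.
- Order is set by simple randomisation (Methods/Design; Procedure), so equal sequence groups are not guaranteed.
- Measurements fall on Days 1, 15 and 29.

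**Assumptions.** Each order has probability 0.5, effects are additive, and there is no carry-over after the washout.

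**Notation.** f is the share with oxygen first, t is the oxygen-minus-APAP effect, and p is the period 2 minus period 1 shift.

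**1. Columns read as periods.** Period 2 minus period 1 averages p − t in the oxygen-first group and p + t in the APAP-first group. Overall:

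f(p − t) + (1 − f)(p + t) = p + (1 − 2f)t

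At 10:10 this difference contains none of the device effect. At 12:8 it contains 20% and at 14:6 it contains 40%, always added to the whole of p.

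**2. Columns read as devices, compared with Day 1.** Elapsed time is 15 − 1 = 14 days for the device used first and 29 − 1 = 28 days for the device used second. Any trend over that time enters each change in full. Between the two devices the shared Day 1 value cancels. Oxygen minus APAP averages t − p in the oxygen-first group and t + p in the APAP-first group. Overall:

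f(t − p) + (1 − f)(t + p) = t + (1 − 2f)p

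The device effect is recovered, with a residue of size |n1 − n2|/N times p.

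**3. Averaging the two sequence means with equal weight.** [(t − p) + (t + p)]/2 = t, whatever the split. The variance relative to a balanced split is N²/(4·n1·n2).

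| Split of 20 | Share of p left in the unadjusted contrast | Probability of this split or worse | Variance factor of the adjusted contrast |
|---|---|---|---|
| 10:10 | 0 | – | 1.00 |
| 12:8 | (12 − 8)/20 = 0.2 | 0.503 | 400/384 = 1.04 |
| 14:6 | (14 − 6)/20 = 0.4 | 0.115 | 400/336 = 1.19 |

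Exact balance has probability 0.176, and the mean absolute share of p over all splits is 17.6%. Among the 10 adults who have lung volumes, 5:5 has probability 0.246. A split of 7:3 or worse, which leaves at least (7 − 3)/10 = 0.4 of p, has probability 0.344.

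**The case against.** The strongest reply is that the baseline-table sentence plainly intends the two orders, so intervention 1 and 2 there mean devices, and the next sentence may well mean reporting by device. The section on adherence uses arm for a device. A device comparison is clearly intended: the Abstract looks for advantages of one intervention over the other, the tie-break requires it, and the Discussion promises statistical evaluation of physiological data. A journal article also leaves models, intervals and table layouts to a fuller plan. All of this stands in part.

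It rules out two stronger readings. A reader might infer that oxygen against APAP will never be estimated. The article does not say so, and the contrast follows from the two changes from Day 1. A reader might also infer that period effects will be taken for device effects. That is a risk and not a stated practice: between devices the shift cancels at 10:10, and because imbalance can fall either way, the bias averages to zero over randomisations. In the one realised sample it need not be zero. Nor is the lack of an untreated control at issue, since that is a design matter. Comparison with Day 1 also has its own use, because most of the laboratory thresholds in Table 4 are defined from baseline.

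The reply does not remove the contradiction, which lies in the printed text. Nor does it make change from Day 1 the right comparison for choosing a device. The absence of a mixed model or a particular table from an article would be no finding. The defect is that the labels conflict and that the one comparison stated does not fit the decision it may serve.

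**Conclusion.** The point holds at moderate severity. The article uses one pair of labels for both periods and devices. Taken as defined, they give an empty baseline group and columns that mix the devices. The comparison it names carries any trend over 14 or 28 days, and the paired device contrast that would inform the tie-break is unstated. If that contrast is taken without period adjustment, it carries 0, 0.2 or 0.4 of any period effect at 10:10, 12:8 or 14:6.

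These fractions rest on additive effects and no carry-over, and the probabilities rest also on equal chances for the two orders. The article gives no size for a period effect, so the bias cannot be put in clinical units. Severity goes no higher because the primary outcome is qualitative, the quantitative analyses are exploratory and mainly descriptive, and in the stated decision rule physiology counts only after preference.

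**What to change.** 1. Name the two groups oxygen-first and APAP-first, and use them for the baseline table.
2. Keep period 1 and period 2 for time, and oxygen and APAP for devices. Tabulate each variable by device, and by sequence and period.
3. Make the main quantitative summary the within-participant value after oxygen minus value after APAP, averaged with equal weight over the two sequences, with a 95% CI.
4. Keep change from Day 1 as description and for safety review.

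The cost is analysis wording only. No new data are needed, and the article reports that recruitment is still open. Compared with a balanced split, the variance of the adjusted contrast rises by a factor of 1.04 at 12:8 and 1.19 at 14:6.

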## Discussion

This is a pilot cross**-**over interventional trial involving children and adults with SCA. Patient and public involvement has been an integral part of this trial and the key outcome is qualitative and dependent on obtaining good quality data to advise on participant feasibility, acceptability and preference. This is being addressed by using a standard interview, which is carried out by a designated psychologist. The development of a pain endpoint is another important outcome and collecting daily measurements is likely to be challenging. This has been addressed by using smartphone technology via an iPad mini, which can connect to wireless networks but does not require a phone contract [38], which is cost**-**effective and should be easier for participants to complete. Assessment of the usefulness of this technology is important as the first outcome measure for the Phase 2 trial, POMS2b, will be average pain intensity during the 2 observation periods and we plan to use the same technology if this proves successful in the pilot. For this pilot study, we are including patients regardless of pain frequency and severity, although it is possible that patients with a significant burden of pain might have a different spread of preferences. In the Phase 2 trial there is a case for including only patients with chronic pain, screened with an appropriate questionnaire for burden of pain [56]. The patient’s experiences and acceptability of both interventions, and statistical evaluation of pain, adverse events, safety data and physiological data will all be taken into account to determine the most acceptable intervention. The most acceptable intervention will be used in the second phase of the larger proof**-**of**-**concept study (POMS2b).

A potential risk is that the participants and their families do not feel adequately supported to agree to recruitment or to continue in their allocated intervention. The sleep physiologist (who will not be blinded to the interventions) will provide easily accessible advice and support. She will routinely call the patient the day after the intervention has started but will also be available to answer additional question during the time of the intervention. Recruitment may also be a challenge but experienced clinical haematologists are co**-**applicants in order to maximise the chance of steadily recruiting participants who will commit to the study and also remember to complete the online pain score at daily bases. The team has experience of similar trials with the same group of participants, for which it has successfully recruited.

The findings from this pilot study will be disseminated to the scientific community, service users and policy**-**makers via submission to an Open Access peer**-**review journal. In addition the patient public involvement representatives are taking the lead to disseminate the findings to the service users.

## Trial status

The trial is still recruiting.

## Abbreviations

APAP: auto**-**adjusting continuous positive airways pressure
CONSORT: Consolidated Standards of Reporting Trials
CPAP: continuous positive airways pressure
CRFs: Clinical Report Forms
HbSS: haemoglobin SS
LDH: lactate dehydrogenase
NIHR: National Institute of Health Research
PEDS**-**QL: Pediatric Quality of Life Inventory TM
POMS2a: Prevention of Morbidity in SCA pilot trial
POMS2b: Prevention of Morbidity in SCA Phase 2 trial
PPI: participants and public involvement
QOL: quality of life
RCT: randomised controlled trial
RfPB: Research for Participant Benefit
SCA: sickle cell anaemia
SpO_2_: oxygen saturation
WISC**-**^IV^UK: Wechsler Intelligence Scale for Children
